### Statistical analysis

This study will employ intention-to-treat (ITT) analysis as the primary analytical approach, with per-protocol (PP) analysis conducted as a sensitivity analysis. The ITT analysis set includes all randomized participants, while the PP analysis set includes participants who completed the full 12-week follow-up with device usage compliance ≥80%. All statistical analyses will be performed using R software version 4.2.0, with significance level set at *α* = 0.05 (two-sided test).

For baseline characteristics analysis, continuous variables will be presented as mean ± standard deviation or median (interquartile range) according to their distribution characteristics, and categorical variables will be presented as frequency (percentage). Between-group baseline comparisons will employ independent samples t-test or Mann–Whitney U test (for continuous variables), and chi-square test or Fisher’s exact test (for categorical variables).

Analysis of primary outcome measures (VD and HD) will employ mixed-effects linear models to account for the correlation of repeated measurements. The model will include fixed effects (treatment group, time point, and their interaction) and random effects (participant), with adjustment for baseline values and pre-specified covariates. Between-group differences will be expressed as least squares mean differences estimated from the model with their 95% confidence intervals.

Secondary outcome measures will be analyzed using different statistical methods. For ordinal categorical variables such as MAS scores and VAS scores, generalized estimating equations (GEE) models with cumulative logit link functions will be used. For continuous variables such as FMA-UE and MBI scores, the same mixed-effects model approach as the primary outcomes will be employed. Secondary outcome comparisons will be adjusted for multiple testing. For the primary analysis, we will apply Bonferroni correction to control family-wise.

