error rate across secondary outcomes. However, given the expected correlation among secondary outcomes (pain, motor function, spasticity)—which may render Bonferroni overly conservative—we will additionally report results using the Holm-Bonferroni procedure (which maintains family-wise error control with less conservatism) and examine false discovery rate for comparative interpretation. Subgroup and sensitivity analyses are designated as exploratory given sample size limitations. Missing data will be handled using multiple imputation based on Markov Chain Monte Carlo (MCMC) methodology. The imputation model includes all baseline covariates (age, time since stroke, baseline GHS severity, stratification factors) and time-varying measurements of primary and secondary outcomes at available timepoints. We assume missing data are missing at random (MAR).

conditional on observed covariates—a reasonable assumption given that dropout is primarily due to logistical constraints (missed appointments) rather than outcome-dependent missingness. Twenty complete datasets will be generated, analyzed separately, and results combined using Rubin’s rules. Sensitivity analyses will assess robustness to departure from the MAR assumption.

This study will also conduct pre-specified subgroup analyses, including stratification by stroke type, baseline degree of GHS, and time from onset to enrollment. These analyses will assess heterogeneity of treatment effects by adding interaction terms between subgroup variables and treatment modality to the primary analysis models. Given sample size limitations, subgroup analysis results will be interpreted as exploratory analyses. To evaluate the robustness of results, a series of sensitivity analyses will be performed, including comparisons of different analysis sets, alternative missing data handling methods, and different statistical models.

The complete statistical analysis plan will be finalized and archived before enrollment of the first patient. The analytical process will be executed by an independent statistician who does not participate in study implementation and data collection.

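### The secondary outcomes are decided by Bonferroni although the plan itself notes that Holm gives the same family-wise control less conservatively; Holm would be the better single rule (minor)

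*Protocol article*

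**What the plan says.** All of this is in the Statistical analysis section of the protocol article. The significance level is "0.05 (two-sided test").

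The main rule is given in a sentence that runs across a break in the text: "For the primary analysis, we will apply Bonferroni correction to control family-wise" and then "error rate across secondary outcomes". The family is therefore the secondary outcomes, and Bonferroni is the rule for them.

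The next sentence explains why more is reported. It says that Bonferroni may be too strict, "given the expected correlation among secondary outcomes (pain, motor function, spasticity"), and continues: "we will additionally report results using the Holm-Bonferroni procedure (which maintains family-wise error control with less conservatism) and examine false discovery rate". The false discovery rate comes third, in a stated role: the plan will "examine false discovery rate for comparative interpretation".

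The Abstract and the Outcome measures section list four secondary outcomes: MAS, VAS, FMA-UE and MBI. The article gives no reason for keeping Bonferroni as the main rule. It does not say what to conclude when an outcome passes Holm but not Bonferroni.

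**The concern.** The plan names a rule that it regards as less conservative with the same protection, and then decides by the other one. If Holm never loses a rejection that Bonferroni makes, the plan pays in power for pain, spasticity, motor function and daily living and receives no stronger family-wise guarantee.

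The second issue is how the results will read. Bonferroni and Holm will sometimes disagree on an outcome, and the report will then carry a formal failure beside a pass under an equally valid rule, with no instruction on how to describe it.

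The reason given for adding Holm also does not fit. Holm makes no use of the correlation between outcomes. Its gain comes from stepping down through the ordered p-values, and in simulation that gain is largest at correlation 0.

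**Working it through.** **Inputs from the protocol article**
- Two-sided level 0.05 (Statistical analysis).
- Family size m = 4: MAS, VAS, FMA-UE, MBI (Abstract; Outcome measures). It would be 5 if MAS were tested separately in its two muscle groups.

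**Inputs that are assumptions**
- The article gives expected differences only for VD and HD (Sample size calculation). Each true secondary effect is therefore assumed to have 80% power at an unadjusted 0.05, which is a noncentrality of 2.8.
- No correlation is given. The main range is 0.3–0.5, with 0–0.7 as a wider check.

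The article states no per-test level or power for this family, so it has no figure to reproduce.

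**Step 1. Thresholds**
- Bonferroni: 0.05/m. For m = 4 every outcome is tested at 0.0125.
- Holm: the i-th smallest p-value is tested at 0.05/(m − i + 1), stopping at the first failure. For m = 4 the levels are 0.0125, 0.0167, 0.025 and 0.05.
- For m = 5: Bonferroni 0.01; Holm 0.01, 0.0125, 0.0167, 0.025 and 0.05.

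Holm's first threshold equals Bonferroni's and its later ones are larger. Two facts follow. Every Bonferroni rejection is also a Holm rejection, and the chance of at least one rejection is identical.

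**Step 2. Bonferroni power by formula**

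Power ≈ Φ(2.8 − z), with z the two-sided critical value.
- Unadjusted: Φ(2.8 − 1.96) = Φ(0.84) = 80%.
- At 0.0125: Φ(2.8 − 2.50) = Φ(0.30) = 62%.

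This does not depend on the correlation or on how many other outcomes respond.

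**Step 3. Holm power by simulation** (four correlated two-sided z tests, correlation 0.3–0.5)

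| Outcomes with a true effect | Bonferroni, mean power per true effect | Holm, mean power per true effect |
|---|---|---|
| 1 | 62% | 62% |
| 2 | 62% | 64% |
| 3 | 62% | 67% |
| 4 | 62% | 71–72% |

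With four true effects, the chance that all four are significant is 25–31% with Bonferroni and 47–53% with Holm. No simulated trial had a Bonferroni rejection that Holm missed.

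**Step 4. A second set of assumptions**

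Here n = 24 per group (30 less the planned 20% dropout), with correlation 0–0.7. One effect size is borrowed from VD, 5.2/6.8 = 0.765 SD; the other is 0.5 SD.
- Four effects of 0.765 SD: 56% with Bonferroni, 64–66% with Holm.
- Two effects of 0.765 SD: 56% and 58–59%.
- Four effects of 0.5 SD: 22% and 25–27%.

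**Step 5. Error control** (same setting as Step 4)
- All four nulls true: Bonferroni and Holm both give 0.049 at correlation 0, 0.043 at 0.5 and 0.036 at 0.7.
- Two effects of 0.765 SD and two nulls: 0.023–0.025 for Bonferroni and 0.033–0.037 for Holm, both below 0.05. Benjamini-Hochberg gives 0.045–0.059, so a false discovery rate result cannot carry a family-wise claim.

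**Step 6. How often the two rules disagree on some outcome** (noncentrality 2.8)
- Two true effects, correlation 0.3–0.5: about 6% of trials.
- Four true effects, correlation 0–0.7: 25–35% of trials.

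**The case against.** **The decision is fixed in advance.** A reader might infer that three procedures leave the verdict to be chosen after the data are seen. The text does not support that. Bonferroni is named as the main rule, Holm is an additional report, and the false discovery rate is for comparison only. This part of the objection stands in full. What remains is the missing guidance on an outcome that passes Holm and fails Bonferroni.

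**The gain depends on how many outcomes respond.** This also stands. The gap of 9–10 points belongs to the most favourable case, in which all four outcomes respond equally strongly. The article's causal model does expect benefit on all four. It also places FMA-UE and MBI downstream of alignment, so equal effects cannot be presumed. With one true effect the gain is essentially nil.

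**Holm has costs.** A reader might infer that the change is free. It is not quite. Bonferroni has simple matching simultaneous confidence intervals and Holm has none that are equally simple, which matters because the plan reports model-based differences with 95% intervals. When some nulls are true, Bonferroni's actual family-wise error is also lower (Step 5). Both rules stay within 0.05, and the article offers neither point as its reason for choosing Bonferroni.

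**The rule is valid as it stands.** Bonferroni errs on the cautious side, so this is an inefficiency and not a mistake in error control. That is correct and limits the severity.

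**Conclusion.** The point holds as a minor improvement. Bonferroni as the main rule is dominated in power by a procedure that the plan already names, at the same nominal family-wise level and under any dependence. That ordering needs no assumption about effects or correlations.

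The size of the loss does rest on assumptions. In the main setting it is about 0, 2, 5 or 9–10 percentage points of mean power per true effect for one, two, three or four responding outcomes, with no change in the chance of at least one rejection.

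The point concerns secondary outcomes only. It implies no inflated error and no open choice of verdict, and it leaves the VD and HD conclusion untouched.

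**What to change.** State that the secondary outcomes (MAS, VAS, FMA-UE, MBI) are judged by Holm at a two-sided family-wise level of 0.05, and that this is the single decision rule. Drop Bonferroni as the main rule. Keep any false discovery rate figure, labelled descriptive. Disagreement between Bonferroni and Holm then no longer needs an interpretation.

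Remove the correlation argument as the reason for Holm. The reason is that Holm is never less powerful at the same family-wise level.

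The sponsor should also say which comparison each outcome contributes to the family. The article lists weeks 4, 8 and 12 alike and names no main visit, so that choice is the sponsor's; the case for Holm is the same whatever the family size.

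The cost is a short edit to the text, with no change to sample size or data collection. The one real loss is the simple matching simultaneous intervals. The 95% intervals for the secondary outcomes should then be described as unadjusted, so that they are not read as reflecting the Holm decision.

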### Ethics and dissemination

This study protocol has been approved by the Ethics Committee of Guangdong Sanjiu Brain Hospital [Ethics Approval No. 2018(02)], and will strictly adhere to the relevant provisions of the Declaration of Helsinki (2013 revision) and the International Ethical Guidelines for Biomedical Research Involving Human Subjects by the Council for International Organizations of Medical Sciences. Patients may withdraw from the study at any time without reason, and this will not affect their routine treatment. Study results will be submitted for publication in peer-reviewed journals within 12 months after completion of the final patient follow-up. Complete reporting will be provided regardless of whether results are positive or negative.

## Discussion

Post-stroke GHS is a common and challenging clinical problem that significantly impacts patients’ rehabilitation progress and quality of life (18, 19). Current research indicates that traditional shoulder slings have obvious limitations in preventing and treating GHS, including insufficient support for the humeral head, poor wearing comfort, and potential exacerbation of shoulder pain (9, 10, 20). Although some recent studies have attempted to improve orthotic design (21–23), these studies have mostly been observational studies or small-sample trials. Based on these issues, we designed this randomized controlled trial with the aim of systematically evaluating the effectiveness of a novel elbow-forearm support orthosis in treating post-stroke GHS through rigorous methodological design and standardized assessment systems.

This study has several significant methodological advantages. First, we employed standardized imaging measurement methods to assess the degree of GHS. By precisely measuring the vertical and horizontal distances from the inferior margin of the acromion to the center of the humeral head, treatment effects can be objectively quantified, avoiding the subjective bias of traditional clinical assessment methods (24). Second, this study established a comprehensive assessment system that includes not only objective imaging indicators but also incorporates clinically relevant indicators such as pain, spasticity, and functional status. This multidimensional assessment approach can more comprehensively reflect treatment effects (25). Third, we adopted a rigorous randomization allocation scheme with outcome assessments completed by independent evaluators, measures that can effectively control selection bias and measurement bias. Additionally, this study utilized the REDCap data management system, achieving electronic and standardized data collection, storage, and monitoring, significantly improving the efficiency and quality of data management. Radiation Safety Considerations: Primary outcome assessment involves radiographic imaging at baseline and weeks 4, 8, and 12. Each shoulder X-ray examination (standard AP view with 15° caudal angle) delivers an estimated absorbed dose of 0.01–0.02 mGy. The cumulative effective dose across the 4 examinations is approximately 0.04–0.08 mSv, which represents 2–3% of the annual background radiation exposure (~2–3 mSv) and remains well below ICRP occupational exposure limits (20 mSv/year). Estimated radiation-associated cancer risk is <0.001%. This level of radiation exposure is justified by the clinical necessity of objective radiographic assessment to rigorously evaluate orthotic efficacy. All participants provided informed consent acknowledging radiation exposure. All radiologic technicians are trained in ALARA (As Low As Reasonably Achievable) protocols to minimize unnecessary exposure. Finally, we developed detailed adverse event monitoring and management procedures, which are of great importance for evaluating the safety of interventions. These methodological advantages enable this study to provide higher-quality evidence-based medical evidence for the treatment of post-stroke GHS.

The mechanisms by which the elbow-forearm support orthosis improves post-stroke GHS may involve multiple aspects. From a biomechanical perspective, this device can effectively counteract the effects of gravity and abnormal muscle tone on the shoulder joint by providing upward support and inward thrust (26). Meanwhile, the device design also considers the biomechanical characteristics of the shoulder girdle, maintaining normal spatial relationships between the acromion and humeral head by limiting scapular downward rotation and anterior tilting (27).

From the perspective of neuromuscular regulation, the elbow-forearm support orthosis may function through multiple mechanisms. First, by providing continuous proprioceptive input, it promotes sensorimotor integration and helps improve proprioception of the affected upper limb (7). Second, the supportive action of the device reduces abnormal traction stimulation, potentially decreasing the degree of spasticity in shoulder muscle groups (28). Furthermore, by maintaining correct shoulder joint positioning, this device creates favorable conditions for functional recovery of the rotator cuff muscles, which is of great significance for preventing and improving GHS (24).

In summary, the elbow-forearm support orthosis may provide a comprehensive solution for treating post-stroke GHS through multiple mechanisms including biomechanical support, neuromuscular regulation, and functional adaptation.

This study also has some potential limitations. First, as a single-center study with a relatively limited sample size, this may affect the external validity of the research findings. Although we control for confounding factors through rigorous randomization and stratified design, the generalizability of the study results still requires further validation through multicenter large-sample studies. Second, considering the heterogeneity of stroke patients, the inclusion and exclusion criteria set in this study may limit the applicability of results to certain specific patient populations. For example, the exclusion of patients with severe cognitive dysfunction may affect the generalizability of study results in this population. Third, although this study employed standardized assessment methods, some functional assessment indicators may still be influenced by evaluator subjective judgment. These limitations suggest that we need to maintain a cautious attitude when interpreting study results, while also providing directions for improvement in future research.
